##### Recruitment of patients

Within each practice, the recruitment of patients is coordinated by practice assistants supported by the GP as needed. To avoid selection bias, practices are requested to list all patients with a diagnosis of essential hypertension in their electronic patient management system. Practices are asked to screen all these patients regarding the inclusion criteria and, if applicable, to ask for study participation during their next routine visit. Each practice follows this approach up to the inclusion of at least 17 patients. Practices are asked to systematically document the recruitment including reasons for non-participation.

##### Changes due to the SARS-CoV-2 pandemic

As described in the “Sample size {14}” section, the pandemic interfered with the recruitment of practices and patients. Thus, a much larger number of practices needed to be contacted to recruit the target number. Also, lock-down periods in Germany from fall to spring 2020/2021 led to dropouts of recruited practices requiring additional practice recruitments. Thus, the total recruitment time had to be extended from 6 months to 12 months in total. Given large regional and inter-practice variations of pandemic burden, practices from both groups were asked to include additional patients if possible, to compensate for practices with lower patient recruitment. Nonetheless, approaches for recruitment of practices and patients remained identical over time.

### Assignment of interventions: allocation

#### Sequence generation {16a}

The randomization is conducted by the independent trial center responsible for data management and monitoring. The allocation sequence is computer-generated based on random numbers. Stratified block randomization (1:1) is used to ensure a balanced distribution of urban and rural localized practices in the intervention and control arm.

#### Concealment mechanism {16b}

For each practice recruited, the trial center will communicate the allocation in written form to the researchers of the Institute of Family Medicine and General Practice.

#### Implementation {16c}

The trial center, which is not involved in recruitment processes, generates the allocation sequence. The Institute of Family Medicine and General Practice enrolls physicians/practices. After a practice is randomized by the trial center, the institute informs the practice about the allocation. All practices enroll patients.

### Assignment of interventions: blinding

#### Who will be blinded {17a}

Blinding of involved scientists, practice personnel, and patients is not possible due to the ICT-based intervention which is offered to the intervention group only. Data analysts will follow predefined standard operating procedures for analysis to avoid bias.

#### Procedure for unblinding if needed {17b}

Not applicable.

### Data collection and management

#### Plans for assessment and collection of outcomes {18a}

Measurement instruments address patients, GPs, and practice assistants. For details on points in time, see Additional File 1: Table S2.

The following are the patients’ measurements:
Blood pressure measurements: All patients receive standardized practice BP measurements by trained practice assistants. For details, see the “Outcomes {12}” section. In the intervention group, only BP measurements from home BP measurements will be analyzed as transmitted electronically to the PIA-PrMC.Mental well-being during the last 14 days is assessed using the WHO-Five Well-Being Index (WHO-5,1998 version, in German) [18–20]. It consists of 5 items on a 6-point Likert scale (5 = “all of the time” to 0 = “at no time”). The scores are added to a sum score ranging from 0 to 25, which is multiplied by 4 to achieve the final score with 0 denoting the worst and 100 representing the best subjective well-being [18].The usability of the PIA-ICT is measured using the standardized and validated System Usability Scale (SUS) which consists of 10 questions on a 5-point Likert scale (1 = “strongly disagree” to 5 = “strongly agree”) [21, 22]. The total score ranges from 0 to 100, with a higher score indicating greater usability. An average SUS score of 70 or more is considered appropriate [22].Medication adherence is measured using the standardized and validated Medication Adherence Rating Scale (MARS-D, German version) [23]. It consists of 5 items on a 5-point Likert scale (1 = “always” to 5 = “never”) which yields a sum score between 5 and 25 points with a higher score indicating better medication adherence [23].Acceptance and use of the PIA-ICT are measured using the Unified Theory of Acceptance and Use of Technology model (UTAUT) which consists of 18 questions on a 5-point Likert scale (1 = “strongly disagree” to 5 = “strongly agree”). It assumes that behavioral intentions (3 items) and effective use of technology are influenced by four determinants for acceptance: performance expectancy (4 items), effort expectancy (4 items), social influence (3 items), and facilitating conditions (4 items) [24, 25].Patients’ characteristics: Sociodemographic characteristics, risk factors (for example, physical activity and smoking behavior), medication adherence, management of BP self-readings, and state of general health are requested. For each patient, the GP completes a sheet addressing the patients’ medical history regarding hypertension, hypertension-related diseases, hospitalizations, other diagnoses, and details on medication and their changes during the study.

The following are the measurements addressing physicians and practice assistants:
Occupational self-efficacy of physicians is measured using a short version of the Occupational Self-Efficacy Scale [26, 27]. The instrument consists of 8 items on a 6-point Likert scale (6 = “totally disagree” to 1 = “totally agree”) with a higher sum score indicating a higher occupational self-efficacy.Sociodemographic and professional characteristics of GPs and practice assistants: age, sex, professional degree(s), additional qualifications, number of years in practice, and working full-time or part-time.Intervention group only: SUS [22] and UTAUT [24, 25] questionnaires as described above (see section 18a, patients’ measurements).Given the SARS-CoV-2 pandemic, two questions were added for physicians and practice assistants addressing the perceived burden due to the pandemic.

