A Cochrane review of various interventions showed the best effects on hypertension control if strategies targeting patients, physicians, and organizations are combined [8]. Recently, complex interventions integrating information and communication technologies (ICT) and delegation to non-physician personnel were successful [9]. Margolis et al. [9] developed an ICT-supported case management involving a delegation model to pharmacists: patients transmitted BP self-monitoring results electronically to a clinical pharmacologist who adjusted drug regimes. After 12 months, intervention effects of − 9.7/− 5.1 mmHg systolic/diastolic were observed; the BP control rate in the intervention group was 18% higher than that in the control group (71% vs 53%) [9]. A meta-analysis of 33 studies on hypertension management delegated to non-physician staff (nurses) showed better BP reductions than standard care (systolic − 8.2 mmHg) [10]. Interventions with nurses who were allowed to prescribe and adjust medications achieved effects of − 8.9/− 4.0 mmHg [10]. Similar results were achieved in a physician-guided, nurse-managed hypertension management which used patient self-measurements and drug algorithms: after only 6 months, an intervention effect of − 8.5/− 3.1 mmHg was observed [11]. This effect was achieved by four times more frequent drug adjustments in the intervention group compared to the control with standard care (*p* < 0.01).

Based on these results, the PIA-Intervention was designed as an ICT-supported case management for the German general practice setting: the PIA-Intervention allows for a highly secured, electronic communication between patients (PIA-App for smartphone/tablet) and practices (PIA practice management center, PIA-PrMC). Patients learn to obtain and transmit reliable BP readings to the practice using the PIA-App; trained practice personnel provide electronic feedback with adjusted medication plans. The concept includes a physician-supervised delegation to practice assistants who manage recall, electronic communication with patients, and step-wise medication adjustments under physician supervision.

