### Eligibility criteria {10}

#### Eligibility criteria on practice level

All of the following inclusion criteria apply: (a) certified GP eligible to serve patients insured in the statuary health insurance, (b) practice is equipped with at least one practice computer with Internet access (Windows 7 or higher), and (c) participation of at least one GP and up to three practice assistants per practice.

The exclusion criteria are as follows: (a) GP has an additional qualification in hypertensiology and/or (b) participated in the development of the intervention.

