**Fig. 2 Fig2:**
[figure not shown]
The elements of the PIA-Intervention

**Table 1 Tab1:** The PIA-Intervention: elements and target groups

	PIA-ICT		PIA-Education		
	PIA-Practice management center (PIA-PrMC)	PIA-App	PIA-eLearning and on-site teaching		PIA-Patient-Education
Setting	Secured system in practice	On patients’ smartphone/tablet	PIA-Website for practices (secured login) and on-site teaching		In practice and PIA-App
Target croup	GPs and practice assistants	Patients	GPs	Practice assistants	Patients
Functions/content	1. Secured patient-practice communication 2. Recall and step-wise medication adjustments 3. Communication GP and practice assistants 4. Pre-defined algorithms for medication regimes 5. Graphic display of BP data and target range over time 6. Electronic transmission of medication plan, physician PIN required 7. Data transfer to the trial center 8. Data download for the practice	1. Secured patient-practice communication 2. Transfer of BP values 3. Display of current medication plan 4. BP history displayed as a graph for different time grids 5. Request for prescription refill	1. Evidence-based information on hypertension 2. How to use the PIA-PrMC 3. Details of the delegation model 4. Information on the study processes	1. Evidence-based information on hypertension including medication classes 2. How to use the PIA-PrMC 3. How to use the PIA-App 4. How to obtain valid BP measurements in practice and at home 5. Information about the study processes	1. How to use the PIA-App 2. How to obtain valid BP measurements (in practice training and video) 3. Access to websites with evidence-based information on hypertension

The concept realizes a physician-supervised delegation model for hypertension management. The PIA-ICT was conceptualized by researchers of the Institute of Family Medicine and General Practice of the University of Bonn. It was realized together with experts for medical informatics from a private company following an agile design. The software solution was piloted in primary care practices with GPs, practice assistants and patients prior to its use in this cCRT.

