#### Strategies to improve adherence to interventions {11c}

Patients in the intervention group will receive an upper arm electronic BP measuring device (BOSO family 4) for use in the study that they may keep afterwards. The PIA practice assistants will analyze the patients’ submitted BP readings at least once a week and will provide appropriate feedback under supervision. Patients not answering to electronic reminders will be contacted by phone if no BP data are transmitted for several weeks. Practices in both study arms will receive financial reimbursement per participating patient.

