#### Primary outcome

The primary outcome is the BP control rate (% of patients with controlled BP). The BP is defined as “controlled” if the practice BP reading is in the target range, i.e., ≤ 140/90 mmHg (calculated as the mean value of the 2nd and 3rd BP readings, 3 successive measurements at intervals of 1 min each in a seated position).

The selected outcome “BP control” is internationally recognized as a surrogate parameter for the prevention of secondary diseases [13]. A meta-analysis of 47 randomized controlled trials with 153,825 patients showed that a BP reduction of 10 mmHg systolic and/or 5 mmHg diastolic reduces the relative risk for major outcomes after 5 years: heart failure by 43%, stroke by 36%, cardiovascular death by 18%, and coronary heart disease by 16% [3].

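### The primary BP reading is taken by unblinded practice assistants, the staff group that delivers the intervention, and no rule keeps the assistant who manages a patient from measuring that patient's outcome

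*Protocol article*

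**What the plan says.** The primary outcome is a yes/no status taken from a practice measurement. Primary outcome: "The BP is defined as “controlled” if the practice BP reading is in the target range, i.e., ≤ 140/90 mmHg". It is the mean of the second and third of three seated readings taken one minute apart.

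Who measures is fixed in {18a}: "All patients receive standardized practice BP measurements by trained practice assistants".

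The same staff group delivers the intervention. Background and rationale {6a} describes a "physician-supervised delegation to practice assistants who manage recall, electronic communication with patients, and step-wise medication adjustments under physician supervision". Strategies to improve adherence {11c} has the assistants review submitted readings "at least once a week and will provide appropriate feedback under supervision". Table 1 lists, in the assistants' training that also covers the PIA software, "How to obtain valid BP measurements in practice and at home".

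On blinding, {17a} states: "Blinding of involved scientists, practice personnel, and patients is not possible due to the ICT-based intervention which is offered to the intervention group only". The only countermeasure named there is standard operating procedures for the data analysts. Implementation {16c} has each practice informed of its allocation.

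On staffing, practice eligibility requires "participation of at least one GP and up to three practice assistants per practice". Two assistants per practice is the planning figure in both sample size sections.

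**The concern.** The people whose work is under evaluation also produce the measurement that judges it, at a cut-off they know. No text separates the two tasks, so in an intervention practice the assistant who has followed a patient's readings for months may also take that patient's final reading. Small, unintended differences in handling matter most near 140/90: rounding down, or starting the series again after a rest. If they occur more in one arm than in the other, they enter the primary comparison directly as apparent benefit. Procedures for the analysts act after the reading has been taken and cannot correct it.

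**Working it through.** **Step 1. Reproduce the planned sample size.** Inputs from Sample size {14} and its pandemic subsection: control rates 65% and 50%, intracluster coefficient 0.055, mean cluster size 15, power 90% and then 80%. The 5% two-sided level is from Statistical methods {20a}.

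- Design effect = 1 + (15 − 1) × 0.055 = 1.77.
- Unpooled formula: n = (z_0.975 + z_power)² × (0.65 × 0.35 + 0.50 × 0.50) / 0.15².
- 90% power: 223.0 × 1.77 = 394.7, so 27 clusters of 15 = 405 per arm. This matches.
- 80% power: 166.6 × 1.77 = 294.8, so 20 clusters of 15 = 300 per arm. This matches.

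The sample size is therefore not in question. The next steps use 300 per arm and 1.77.

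**Step 2. From mmHg to control rate (assumed inputs).** The documents give no distribution of follow-up BP. Assume normal systolic BP centred at 140 mmHg, which gives a 50% control rate, with SD 12, 15 or 18, and ignore diastolic BP. Reading s mmHg lower in one arm moves the control rate by Φ(s/SD) − 0.5:

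| Shift | SD 12 | SD 15 | SD 18 |
|---|---|---|---|
| 1 mmHg | 3.3 points | 2.7 | 2.2 |
| 2 mmHg | 6.6 points | 5.3 | 4.4 |

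A second route gives the same range. The share of patients between 140 and 144 mmHg is 13.1%, 10.5% and 8.8% for SD 12, 15 and 18. If half of them were recorded as controlled in one arm only, the shift would be 6.6, 5.3 and 4.4 points.

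**Step 3. From control rate to type I error.** With no true effect and 50% control in both arms:

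- SE = √(2 × 0.25 × 1.77 / 300) = 0.0543.
- Rejection probability with artefact b = P(|Z + b/SE| > 1.96).
- b = 0: 5%. b = 0.03: 8.6%. b = 0.05: 15.1%.

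**Step 4. What the text does and does not establish.**

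- Established: readers are unblinded practice assistants; practice assistants deliver the intervention; no rule separates the two tasks.
- Not established: which assistant measures which patient; that every practice has a second assistant, since eligibility sets only an upper limit of three; the size or direction of any bias.

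**The case against.** The protocol is open about the lack of blinding and is not careless about measurement. Three timed seated readings, with the second and third averaged, leave little room to choose which values count. Readers are trained, and independent monitors audit the study folders at baseline and follow-up. Numeric BP is retained, because change in systolic and diastolic BP is a listed secondary outcome. All of this stands and limits the risk. It does not prevent rounding or a restarted series, and a folder audit checks documentation, not how a reading was taken. A differential shift in the readings would also carry into the numeric outcome.

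A second assistant is a weak remedy. Allocation is by practice, so that assistant knows the arm, may have had the same training and may manage other study patients. This also stands: what is removed is the personal stake in one's own patient, not knowledge of allocation.

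The decisive input in the illustration, an error occurring in one arm only, has no support in the documents. That is correct, and the figures are offered only as an illustration.

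Form fields and sensitivity analyses commonly belong to the case report form and the SAP. That is fair, so they appear below only as support. Who measures the primary outcome is a design matter that {18a} itself settles, and the article calls itself the full study protocol in {31c}.

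**Conclusion.** The point holds as an avoidable bias risk that existing staff can reduce. The primary outcome rests on readings by unblinded members of the group that delivers the intervention, and nothing keeps a patient's case manager from taking that patient's follow-up reading.

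A reader might infer more than the text supports:

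- That the managing assistant does take the reading. The protocol does not say so; it only fails to exclude it.
- That every practice has a spare assistant. Two is the planned number, not an entry requirement.
- That using the other assistant would blind the assessment. It would not.
- That the trial has a type I error of 15%. The range of about 9–15% applies only if an artefact of 3 to 5 points arises in one arm, with 50% control in both arms, 300 patients per arm and design effect 1.77.

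Neither the actual size of the bias nor the part that role separation would remove can be derived from the documents.

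One sentence in {18a} needs separate attention. Directly after the quoted rule, it says that in the intervention group only home measurements will be analysed. Taken literally, the assistants' readings would then not decide that arm's outcome, which conflicts with the Primary outcome section. It may be a misplaced word, but the two places must be reconciled.

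**What to change.** In {18a}, add:

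1. Where a practice has two or more participating assistants, the follow-up readings are taken by one who did not do that patient's case management. In control practices, they are taken by one not mainly responsible for that patient's BP care. Practices with a single participating assistant are exempt.
2. The reader's role is recorded with the reading.
3. A statement that this separates delivery from measurement but does not blind the assessment, and that this remains a limitation.

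In support, in the case report form or SAP: the trial center derives the mean and the control status from the three recorded readings. End-digit preference and heaping just below the cut-off are reported by arm, with a sensitivity analysis of the primary endpoint at nearby cut-offs.

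Reconcile the home-reading sentence in {18a} with the Primary outcome section.

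Cost: some scheduling in practices already strained by the pandemic, one form field and a small set of additional analyses. No extra staff or visits are needed. Recruitment was scheduled to run to March 31, 2021, with at least 6 months of intervention, so for patients recruited late the rule can be in place before the follow-up reading.

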PIA-App for patients (PIA-App): The PIA-App is a patient-facing application for smart devices (smartphone or tablet with Android operating system) that allows a secured communication between patient and practice. The key communication feature is the transmission of BP readings from the patient to the practice and the transfer of adjusted medication plans from the practice to the patient, paralleled by short text messages in both directions. The patient receives a push notification when the practice has sent a new medication plan. To motivate patients’ adherence, a graph displays BP data over time including systolic BP (SBP), diastolic BP (DBP), pulse rate, and the BP target range. The BP target is set at < 135/85 mmHg per standard but can be individualized by the GP. In addition, the PIA-App enables patients to request prescription refills and access to a video on how to obtain a valid BP measurement as well as web links related to hypertension.PIA practice management center (PIA-PrMC): The PIA-PrMC is a Windows application, which is used by GP and practice assistants to manage patients’ hypertension therapy. It allows for reviewing patients’ BP records and to adjust drug regimes. Integrated into the application, processes realize a delegation model: First, the GP enters his individual preferences regarding medication regimes. These can be individualized as needed for each patient. Second, the practice assistant reviews the incoming BP readings and—as long as target BP values are not reached and medication is tolerated—adjusts the pre-set medication regime and writes a suggestion for a short note to the patient. Third, the GP reviews these suggestions and, if approved, initiates the electronic transmission to the patient’s PIA-App using a physician personalized identification number (PIN). If a GP does not agree with the practice assistants’ suggestions and prefers a different medication regime or text message, the physician communicates this to the practice assistant who executes these physician orders with identical subsequent procedures. Fourth, the PIA-PrMC supports the electronic recall of patients who did not transmit BP readings or have questions regarding their BP care.The medication options offered to GPs follow the current hypertension guidelines as issued by the European Society of Hypertension [2]. For convenience, pharmaceutical agents are displayed according to the regional prevalence of their use in previous years. For each pharmaceutical agent, a typical regime for step-up dosing is integrated, thus allowing for an advanced treatment plan for each patient. In case of adverse drug reactions or other needs to adjust medication choices, the patient’s medication plan can be adjusted individually by the GP.Data management for the study is facilitated by an export function of aggregated, pseudonymized data in a data file format.PIA-eLearning for GPs and practice assistants:*PIA-eLearning for physicians*: An audio-visual learning video with about 35 slides introduces GPs to the PIA-Intervention: how to use the software and the delegation concept with the new role for practice assistants (PIA practice assistant) within the German legal frame. The latter allows for the delegation of specific tasks to practice assistants and nurses, but not substitution, i.e., no issuing of prescriptions and no independent medication adjustments.*PIA-eLearning and PIA certificate to qualify practice assistants (PIA practice assistant)*: Audio-visual learning videos with about 50 slides and a video on BP self-measurements trains practice assistants on the following topics: how to measure BP according to standard, hypertension as so-called silent killer, sequelae of untreated hypertension, BP targets, drug regimens according to guidelines, how to implement the medication step-up based on physician-defined algorithms, short text message communication via the PIA-PrMC, patient management, and recall using the PIA-PrMC. In addition, practice assistants learn how to conduct the study at their practice site and how to educate patients regarding home BP readings. After the eLearning, practice assistants take a written examination and, if passed, receive the PIA certificate. eLearning material will be provided for download via a secured web space.4.PIA in-practice and in-app education of patients: After informed consent and study inclusion, the PIA practice assistant will teach each patient individually how to obtain valid BP readings and how to use the PIA-App including the in-app video on valid BP home measurements and further web links.

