### Outcomes {12}

The following primary and secondary outcomes will be analyzed for each patient, both study groups (intervention, control) and the total population, if appropriate.

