#### Secondary outcomes

The following are the secondary outcomes: (1) changes of SBP and DBP practice measurements per patient, (2) medication use and changes over time (number, kind, and dosing of antihypertensive medications used), (3) frequencies and kind of cardiovascular events (myocardial infarction, stroke, other) or death within the study period, (4) number of hospitalizations (emergency room treatments and/or in-hospital stays) and their causes care, (5) quality of life, (6) patients’ satisfaction regarding hypertension treatment by GP practice, (7) time to BP control, (8) patients’ health literacy, (9) medication adherence, (10) perceived time to invest for hypertension management in general (by physicians, practice assistants, and patients) (e.g., estimated duration of office consultation including waiting time, BP measurements, and prescription refills), (11) number of physician consultations and practice visits, and (12) perceived workload of the GPs and practice assistants by hypertension management and, for the intervention group only, (13) number of contacts between the practice assistant and patients via PIA-ICT including use of safety functions if applicable and (14) satisfaction and acceptance of PIA-Intervention by patients, GPs, and practice assistants. For details on time points, see Additional File 1: Table S2.

The following secondary data will be provided for patients insured in the respective statutory health insurance, which is a consortium partner: (1) emergency room treatments, (2) hospitalizations (e.g., in-hospital days), (3) prescription details, and (4) death (date and cause of death).

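### Read literally, the data-collection section restricts intervention-arm BP analysis to home readings, contradicting the practice-BP outcomes defined for both groups

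*Protocol article*

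**What the plan says.** In the protocol article, the section Primary outcome counts BP as controlled "if the practice BP reading is in the target range, i.e., ≤ 140/90 mmHg". The value is the mean of the second and third of three seated readings, and the arms are not distinguished. The opening of Outcomes {12} states: "The following primary and secondary outcomes will be analyzed for each patient, both study groups (intervention, control) and the total population, if appropriate". The first item under Secondary outcomes is "changes of SBP and DBP practice measurements per patient", so the BP-change outcome also rests on practice readings.

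Plans for assessment and collection of outcomes {18a} begins consistently: "All patients receive standardized practice BP measurements by trained practice assistants", with a pointer back to Outcomes {12}. The next sentence in the same bullet reads: "In the intervention group, only BP measurements from home BP measurements will be analyzed as transmitted electronically to the PIA-PrMC".

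Two further places bear on the point. Intervention description {11a} says of the patient app: "The BP target is set at < 135/85 mmHg per standard but can be individualized by the GP". Secondary outcomes also lists "7) time to BP control" ahead of the items reserved for the intervention group, without saying which readings define the event.

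**The concern.** Section {18a} is where the protocol says how BP is assessed. Its sentence on the intervention group does not limit itself to secondary or descriptive use. Taken as printed, it leaves home readings as the only analysable BP in one arm, while the other arm has practice readings. The two arms would then differ in setting, in who takes the measurement and in how often it is taken, as well as in treatment. A difference in control rate could arise with no treatment effect, and randomization does not protect against that.

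The wording matters more here because Who will be blinded {17a} says that scientists, practice staff and patients cannot be blinded, and relies on predefined procedures to keep the analysis free of bias. The written rule on which measurement counts therefore has to be unambiguous.

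**Working it through.** **1. The passages side by side.**

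| Place in the protocol article | BP source | Arms |
|---|---|---|
| Outcomes {12}, opening | not specified | both |
| Primary outcome | practice | no distinction |
| Secondary outcomes, item 1 | practice | no distinction |
| {18a}, first sentence on BP | practice | all patients |
| {18a}, sentence on the intervention group, as printed | home only | intervention |

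The last row cannot stand with the other four. If the comma is moved so that the sentence opens with *in the intervention group only*, the conflict disappears: home BP becomes an extra dataset that exists in one arm. That reading fits {11a}, where the app belongs to the intervention, and {11c}, where the study BP device goes to intervention patients.

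**2. The plan's own sample-size figures.** Inputs from Sample size {14} and its pandemic subsection: 65% vs 50%, ICC 0.055, mean cluster size 15, unpooled two-sided Z-test. The 5% two-sided level is from {20a}.

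Design effect = 1 + (15 − 1) × 0.055 = 1.77.

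n per arm = (z_0.975 + z_power)² × (0.65 × 0.35 + 0.50 × 0.50) / 0.15², times 1.77.

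- 90% power: 223.0 × 1.77 = 394.7; 394.7 / 15 = 26.3, rounded up to 27 clusters, 405 patients per arm.
- 80% power: 166.6 × 1.77 = 294.8; 294.8 / 15 = 19.7, rounded up to 20 clusters, 300 patients per arm.

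Both stated figures reproduce. Neither depends on the disputed sentence.

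**3. Illustration of the literal reading.** These assumptions are not in the documents:

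- no true effect, and 50% practice control in both arms;
- normally distributed systolic BP, with diastolic ignored;
- 140 mmHg applied to home readings in the intervention arm;
- home systolic 5 mmHg lower than practice systolic, inferred from the 135 app target against the 140 practice threshold;
- SD of 12, 15 or 18 mmHg.

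Apparent intervention control rate = Φ(5 / SD). Spurious difference D = Φ(5 / SD) − 0.50. With p = Φ(5 / SD) and 300 patients per arm, SE = √{[p(1 − p) + 0.25] × 1.77 / 300}. The chance of a significant result is Φ(D/SE − 1.96) + Φ(−D/SE − 1.96).

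| SD (mmHg) | Apparent control rate | Spurious difference | Chance of p < 0.05 with no effect |
|---|---|---|---|
| 12 | 66.2% | 16.2 points | about 86% |
| 15 | 63.1% | 13.1 points | about 69% |
| 18 | 60.9% | 10.9 points | about 53% |

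For offsets of 3 to 8 mmHg over the same SDs, the spurious difference runs from about 7 to 25 points.

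**4. Sensitivity to the threshold.** If home readings were judged against 135 instead of 140, the same assumptions give Φ((5 − 5) / SD) − 0.50 = 0. The average offset cancels, although the arms would still be measured differently. The size in step 3 therefore depends on 140 being kept for home readings, which no section states.

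**The case against.** A reader might infer that the primary comparison is in fact planned on different measurements in the two arms. The documents do not support that. The same bullet in {18a} first gives practice BP to all patients and refers to Outcomes {12}. The primary outcome is explicitly practice BP. The statistical methods for the primary endpoint do not bring in home readings. The literal sense would discard practice readings that the bullet has just said every patient receives. The phrase *intervention group only* is used elsewhere, in Secondary outcomes and in the staff measurements, to mark extra data in one arm. A misplaced comma is the likelier explanation.

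A reader might also take the 11 to 16 points as an estimate of bias in this trial. They are not. The protocol gives a default app target that the GP may change. It does not say that home BP reads 5 mmHg lower than practice BP.

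Finally, a reader might conclude that time to BP control is biased by design. Secondary outcomes does not say which readings define the event and refers time points to Additional File 1: Table S2, which is not shown. Nor does the protocol say that control patients have no home device, only that the study supplies one to intervention patients.

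All three objections stand as limits. None removes the contradiction in the printed text. Section {31c} describes the article as the full study protocol, and nothing shown says which statement prevails.

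**Conclusion.** The sentence in {18a} is wrong as written. It contradicts the practice-BP definition of the primary outcome and of the systolic and diastolic change outcomes in both groups. It is most likely a punctuation slip, so this is a wording conflict to be corrected and not evidence that a biased comparison is intended.

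The conflict still deserves correction before analysis, because it concerns which measurement decides the confirmatory test. Followed literally, and under the stated assumptions (5 mmHg inferred offset, SD 12 to 18 mmHg, systolic only, 140 mmHg kept for home readings, 50% true control), the artefact would be about 11 to 16 points, comparable with the planned 15. The sample-size figures are unaffected.

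For time to BP control the point holds only as a consequence of the same sentence. If home readings defined the event in the intervention arm, where {11c} has them reviewed at least weekly, and practice readings defined it in the control arm, the more often observed arm would tend to reach the event sooner.

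**What to change.** Replace the sentence in {18a} with:

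> The primary outcome and the SBP/DBP change outcomes use the standardised practice measurements (mean of 2nd and 3rd readings) in both arms; in the intervention group only, transmitted home readings are additionally analysed, descriptively.

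State also that any between-arm analysis of time to BP control uses practice readings in both arms. Make the analysis plan agree on both points.

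The cost is small. This is a wording change that uses practice readings already planned for all patients, and it leaves the primary outcome definition and the sample size as they are. The one real loss is that time to BP control, if compared between arms, becomes coarser because it is tied to practice measurements.
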